### Statistical analysis

2.10

Efficacy evaluation will be determined by full analysis set and per-protocol set, and safety evaluation will be based on safety set. Statistical evaluation of full analysis set will follow intent-to-treat principles. Last observation carried forward method was used to estimate missing values of major variables. The collected data were statistically analyzed by SPSS 22.0 software. Chi-square test was used for enumeration data; mean value ± standard deviation ($\bar{\text{x}}$ ± S) was used for measurement data, independent sample *t* test was used for normal distribution, and Mann-Whitney *U* test was used for skewed distribution. When *P* < .05, the difference was considered statistically significant.

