**Figure 1 F1:**
[figure not shown]
Flow diagram of this clinical trial.

**Table 1 T1:** Study schedule.

	Screening period	Treatment period		Follow-up		
--Project Stage	Baseline	1-wk	2-wk	1-mo	2-mo	3-mo
Record fill	√					
Fulfill inclusion criteria and exclusion criteria	√					
Sign informed consent	√					
Random allocation	√					
Treatment	√	√	√			
Effectiveness observation						
Cardiac function	√		√			√
Blood lipid levels	√		√			√
The number of angina attacks per week	√	√	√	√	√	√
Total amount of nitroglycerin tablets	√		√			√
Safety evaluation						
Blood test and urinalysis	√		√			√
Liver and kidney function	√		√			√
Record of adverse event		√	√	√	√	√

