#### Shedding criteria and management

2.3.4

Patients who appear severe adverse events or other complications and special physiological changes. The trial should be stopped and corresponding treatment should be given according to the judgment of the investigator;If the subject's condition does not improve or even deteriorate to a certain extent within a certain period of time, although the required follow-up had not been completed, the subject should be withdrawn from the study and received other effective treatments in order to protect the subject;Patients who have poor compliance, change medications or add non-prescribed medications, which may affect the result of the study;Patients who are unwilling or impossible to continue the clinical trial for any reason, and suspend the test by requesting the investigator to withdraw from the test;Patients who are misdiagnosed, or accidentally included without meeting the inclusion and exclusion criteria.

For patients who dropped out of the trial or lost to follow-up, researchers should take active measures to complete the last test as far as possible, so as to analyze its efficacy and safety, and take corresponding treatment measures. All shedding cases should be recorded on the case report form (CRF), and filled in the cause.

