### Sample size

2.4

The sample size was estimated based on the mean and standard deviation of the left ventricular ejection fraction (LVEF) scores of patients 14 days after treatment. Based on the results of the preliminary experiment, the LVEF score was 53.13 ± 6.18 in the treatment group and 49.78 ± 5.78 in the control group. α = 0.025, one-tailed test, β = 0.20. The PASS15.0 software calculated that 49 participants were required for each group, with an estimated drop-out rate of 10%, 55 patients would be enrolled in each group.

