### Outcomes

2.7

Cardiac function: Color Doppler ultrasonography (GE-VIVID7, US) was used before and after treatment and during follow-up time to detect patient's left ventricular end-diastolic diameter, left ventricular end-systolic diameter, and LVEF.Blood lipid levels: Fasting vein blood was collected in the morning before and after treatment and during follow-up time, and automatic biochemical analyzer (HITEC-7100, Japan) was used to detect blood lipid indexes of the patients, including total cholesterol; triacylglycerol; low density lipoprotein cholesterol; high-density lipoprotein cholesterol.The number of weekly attacks of angina pectoris; total amount of nitroglycerin tablets taken during the study period.

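### LOCF is the only stated missing-data method, and with echo and lipids at only three visits it can enter the pre-treatment value as the day-14 result; replace it as the main method

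*Protocol article*

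**What the plan says.** Section 2.10 (Statistical analysis) gives one rule for missing data: "Last observation carried forward method was used to estimate missing values of major variables". The same section says "Statistical evaluation of full analysis set will follow intent-to-treat principles". It also plans a per-protocol analysis and compares groups by independent-sample *t* test, or by Mann-Whitney *U* test for skewed data. It names no other missing-data method.

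In Table 1 the row "Cardiac function" is ticked at baseline, week 2 and month 3 only, and so is the row for lipids. Section 2.7 (Outcomes) agrees: ultrasonography "was used before and after treatment and during follow-up time to detect patient's left ventricular end-diastolic diameter" and the other echo measures. No echo falls between baseline and the end of the 14-day course.

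Section 2.4 (Sample size) rests on the "left ventricular ejection fraction (LVEF) scores of patients 14 days after treatment": "the LVEF score was 53.13 ± 6.18 in the treatment group and 49.78 ± 5.78 in the control group". It arrives at 49 per group and then, "with an estimated drop-out rate of 10%, 55 patients would be enrolled in each group".

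Section 2.3.4 (Shedding criteria and management) withdraws, among others, a subject whose condition "does not improve or even deteriorate to a certain extent within a certain period of time". It also tells staff to try to complete a last test in patients who drop out or are lost.

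**The concern.** LOCF needs a recent on-study value to carry. Here, for day 14, there is none. Unless a final echo is obtained at withdrawal, the only earlier LVEF is the pre-treatment one, so the patient enters the intent-to-treat comparison with a change of exactly zero. For month 3, LOCF assumes that nothing changes over the three months after infusion ends.

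Two things are at stake. First, raising 49 to 55 treats drop-outs as patients who contribute nothing and leaves the 3.35-point difference intact. The full analysis set instead keeps them with a no-change value, which dilutes the difference. Second, some withdrawals are triggered by a poor course. If withdrawal rates differ between arms, and LVEF moves on the background therapy that all patients receive, LOCF produces a difference with no drug effect behind it. The direction depends on which arm loses more patients, so LOCF cannot be defended as conservative.

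**Working it through.** **Inputs from section 2.4.** Means 53.13 and 49.78, so the difference is 3.35. SDs 6.18 and 5.78, so pooled SD = √[(6.18² + 5.78²)/2] = 5.98. One-sided α = 0.025, β = 0.20, 49 evaluable and 55 enrolled per arm, 10% drop-out.

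**Assumed, because the article does not give them.** Baseline LVEF has a common mean in both arms and SD 5.98. The gain on background therapy is 0 to 4 points. The share missing at day 14 and its split by arm are varied. The simulations use a baseline-to-day-14 correlation of 0.6.

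**1. The plan's own figure.** n = (6.18² + 5.78²)(1.960 + 0.842)²/3.35² = 50.08, so 51 per arm against 49 stated, which is close enough. 49/0.90 = 54.4, so 55, as stated. Two-sample *t* test power is 78.3% with 49 observed per arm and 82.9% with 55 and nothing missing. The fair comparator for LOCF is therefore 78.3%.

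**2. Equal drop-out, baseline carried forward.** With a share m missing in each arm and a common baseline mean, the expected difference is (1 − m) × 3.35. The SD comes from the mixture of observed and carried values and grows with the background gain. *t* test power at 55 per arm:

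| Missing at day 14 | Expected difference | SD unchanged | Mixture SD, gain 0 | Mixture SD, gain 3 |
|---|---|---|---|---|
| 10% | 0.90 × 3.35 = 3.015 | 74.5% | 73.9% | 71.9% |
| 5% | 0.95 × 3.35 = 3.18 | 78.9% | 78.6% | 77.6% |

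Simulation (100,000 runs per setting) agrees: 71.9% and 74.0% at 10% missing, 77.6% and 78.8% at 5%, for gains of 3 and 0.

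**3. Unequal drop-out, no drug effect.** Expected bias = −(m_treatment − m_control) × gain. In simulation at 55 per arm:

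| Drop-out, Danhong v placebo | Gain (assumed) | Bias | Two-sided rejection (nominal 5%) | Rejection favouring Danhong (nominal 2.5%) |
|---|---|---|---|---|
| 15% v 5% | 3 | −0.3 | 5.8% | 1.3% |
| 5% v 15% | 3 | +0.3 | 5.8% | 4.4% |
| 20% v 5% | 4 | −0.6 | 8.0% | 0.6% |
| 5% v 20% | 4 | +0.6 | about 8% | about 7% |

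**4. Standard errors.** With 10% missing in each arm, a 3-point gain and no drug effect, the mean standard error reported by the *t* test is 1.15, the empirical standard error is 1.15, and the rejection rate is 5.0%.

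**The case against.** The strongest case for the plan has five parts.

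- **The last test.** Section 2.3.4 asks staff to obtain a final test in patients who leave. Where that succeeds, LOCF carries an on-study echo, not the baseline value. This stands, and it limits the problem to patients with no post-baseline echo. The instruction applies only as far as possible, so some such patients must be expected.
- **Timing of drop-out.** The 10% has no time point, and the study runs for 14 days plus 3 months. If about half of the drop-outs come after day 14, power at day 14 stays near the plan's own level. This also stands, and it is why the 5% row is shown.
- **Unstated details.** The article does not say whether baseline may be carried forward, who enters the full analysis set, or which variables count as major. A fuller document may settle this. LVEF is taken as major because the sample size rests on it. Leaving patients without a post-baseline echo out of the set would remove the dilution but weaken the stated intent-to-treat analysis.
- **The per-protocol analysis.** It is planned, but it would typically leave out the same patients, so it does not answer the question.
- **The replacement.** A repeated-measures model and standard multiple imputation assume data missing at random, so neither alone removes bias from outcome-related withdrawal. This is right, and it is why a sensitivity analysis belongs in the fix.

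A reader might also infer that, because imputed values are treated as observed, the standard errors are wrong. For the planned two-sample test at a single visit this does not hold. A carried-forward baseline is a real measurement, independent between patients, and step 4 shows the *t* test is correctly calibrated under equal drop-out. The fault lies in what is being estimated.

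**Conclusion.** The concern holds at moderate size and should be fixed. LOCF is the only stated method for the full analysis set, and the visit schedule leaves it only the pre-treatment value to carry to day 14 when no final test is obtained.

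The power loss is about 4 to 6 points against 78.3% if the whole 10% is missing at day 14 in both arms, and close to nothing at 5%. It is not a fall from a firm 80%, because 49 per arm does not quite reach that by the *t* test.

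The possible bias matters more because its sign is unknown: about 0.3 points in the milder scenario and 0.6 in the extreme one. A reader might take the 8% error rate as the expected one. The document does not support that: it needs 20% v 5% drop-out by day 14 and a 4-point background gain, and the article states neither. Nor does LOCF necessarily favour Danhong; more drop-out on Danhong than on placebo works against it.

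**What to change.** Make one of these the main full-analysis-set method for LVEF and lipids:

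- a baseline-adjusted, likelihood-based repeated-measures model using the week-2 and month-3 values; or
- multiple imputation by arm, using baseline and all observed visits, including any echo obtained at withdrawal.

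Add one sensitivity analysis aimed at outcome-related withdrawal, for example control-based imputation, because both main options assume missing at random. Keep LOCF, if at all, as a secondary analysis, and state whether a baseline value may be carried forward in it. Settle this before unblinding.

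The cost is analysis wording and a little programming. SPSS 22, the named software, has linear mixed models, and multiple imputation if that module is licensed. No patients or visits are added.

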### Intervention measures

2.6

According to *2014 American College of Cardiology/American Heart Association Guidelines for the Diagnosis and Treatment of Non-ST-Segment Acute Coronary Syndrome*, all patients would receive dual antiplatelet therapy (aspirin 100 mg/d +clopidogrel 75 mg/d) and anticoagulant therapy (unfractionated heparin). And they would also receive statins, angiotensin converting enzyme inhibitors, beta-blockers, and nitrates according to the guidelines.^[18]^ All of these basic treatments will be detailed on the patient's medical record and CRF.

The treatment group was treated with Danhong Injection (Danhong Pharmaceutical Co., Ltd., Shandong, China), 40 ml/d combined with 0.9% normal saline, 250 ml/d intravenously, and the control group was treated with placebo (0.9% normal saline), 40 ml/d, combined with 0.9% normal saline, 250 ml/d, intravenously. All patients received standard treatment for 14 days.

When angina attacks, patients were instructed to take nitroglycerin tablets (Yimin Pharmaceutical Co., Ltd., Beijing, China), 0.5 mg/time, repeated every 5 minutes until angina relieved. Timing and dosage would be recorded in detail on the Case Report Form.

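### Continuous outcomes are compared without baseline adjustment although baseline LVEF, diameters and lipids are measured in every patient: a valid analysis that gives away precision at no saving

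*Protocol article*

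**What the plan says.** Section 2.10 (Statistical analysis) fixes the between-group tests. For counts, "Chi-square test was used for enumeration data". For measurement data the rule is an independent-samples t test or a rank test according to distribution: "test was used for normal distribution, and Mann-Whitney" U for skewed data. No covariate, model or change score is named. The section does not say which outcome is expected to take which test.

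The baseline values exist. Section 2.7 (Outcomes) says echocardiography "was used before and after treatment and during follow-up time", and describes fasting lipids in the same way. Table 1 schedules cardiac function and lipids at baseline, 2 weeks and 3 months.

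Section 2.4 (Sample size) bases the calculation on "left ventricular ejection fraction (LVEF) scores of patients 14 days after treatment", a post-treatment level: "the LVEF score was 53.13 ± 6.18 in the treatment group" and "49.78 ± 5.78 in the control group". It uses no baseline value or correlation. Section 2.5 describes 1:1 central allocation and mentions no stratification by baseline LVEF or lipids.

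**The concern.** A patient's LVEF or LDL cholesterol after two weeks is likely to resemble the value at entry. An analysis that ignores the entry value treats this predictable variation as noise. With about 50 patients per arm and no stratification described, the arms can also differ somewhat at entry by chance, and an unadjusted comparison does nothing to remove that difference.

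A second issue is the rule for choosing the test. If LVEF is judged skewed, the analysis becomes a rank comparison, although the trial was sized on a difference in means. Seven echo and lipid variables are measured at two post-baseline visits, so different outcomes, or the same outcome at different visits, could end up with different effect measures.

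**Working it through.** **Inputs.** From section 2.4: means 53.13 and 49.78, SDs 6.18 and 5.78, one-sided alpha 0.025, power 80%, 49 evaluable and 55 enrolled per group. Assumed: baseline to day-14 correlation r = 0.3, 0.5 or 0.7, and a baseline SD equal to the day-14 SD. The protocol gives neither.

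**Effect size.** Difference = 53.13 − 49.78 = 3.35. Pooled SD = √[(6.18² + 5.78²)/2] = 5.983. Standardised effect = 3.35/5.983 = 0.560.

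**The plan's own figure.** n per group = 2 × (1.960 + 0.842)² / 0.560² ≈ 50.1, so 51 by normal approximation, against the stated 49. That is within two patients, and it confirms that the trial was sized as an unadjusted two-sample comparison. Dropout: 49/0.9 = 54.4, so 55, as stated.

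**Unadjusted power at 49 per group.** SE of the difference = 5.983 × √(2/49) = 1.209. Then 3.35/1.209 = 2.771, and Φ(2.771 − 1.960) = 79.1%. The noncentral t distribution gives 78.3%.

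**Power with baseline adjustment.** The residual SD becomes 5.983 × √(1 − r²), with 49 per group:

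| r | 1 − r² | Power, normal | Power, t | n per group for 80% (normal) |
|---|---|---|---|---|
| 0 | 1.00 | 79.1% | 78.3% | 51 |
| 0.3 | 0.91 | 82.8% | 82.0% | 46 |
| 0.5 | 0.75 | 89.2% | 88.6% | 38 |
| 0.7 | 0.51 | 97.3% | 97.0% | 26 |

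**Chance imbalance.** With the assumed baseline SD of 5.98 and 49 per group, the baseline difference between arms has SE 1.21 points (95% range about ±2.4). Only r times a baseline imbalance is expected to carry into the day-14 comparison. A 1-SE imbalance therefore shifts the unadjusted difference by:

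- r = 0.3: 0.3 × 1.209 = 0.36 points, 11% of 3.35
- r = 0.5: 0.5 × 1.209 = 0.60 points, 18%
- r = 0.7: 0.7 × 1.209 = 0.85 points, 25%

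**If changes were tested instead.** With equal SDs, the variance of a change is 2(1 − r) times that of the level: 1.40, 1.00 and 0.60 at r = 0.3, 0.5 and 0.7. ANCOVA has 0.91, 0.75 and 0.51. A change score is thus less efficient than ANCOVA at each of these values, and worse than no adjustment when r is below 0.5.

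**Choosing the test by shape.** A simulation with no treatment effect and 49 per group used Shapiro-Wilk in each arm to choose between t and Mann-Whitney. The rejection rate at the 5% level was 5.1% for normal data and 4.8% for lognormal data.

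**The case against.** The strongest reply is that nothing here is an error. In a 1:1 randomised trial the unadjusted test is unbiased, its standard error already allows for chance imbalance, and it matches the way the trial was sized. If all 55 enrolled patients per arm are analysed, unadjusted power is about 83% (82.9% by t). At r = 0.3 the gain from adjustment at 49 per arm is only about 4 points, and the larger gains rest wholly on assumed correlations. All of this stands, and it limits the point to an improvement.

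The text also does not say whether the tests are applied to post-treatment values or to changes. Section 2.4 points to post-treatment values, but that is an inference. It would therefore go too far to say that baseline is certainly unused. The recommendation survives either way, because ANCOVA is at least as efficient as both alternatives.

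The analysis plan, which is not shown, may well set the normality criterion, transformations and covariates, and their absence from an article is no fault. But this article does more than stay silent: it states the tests, and those are what the point addresses. Mann-Whitney also has a natural use for weekly angina attacks and nitroglycerin tablets.

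Three stronger readings are tempting and not supported:

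- A reader might infer that a baseline imbalance passes in full into the result. Only r times it does.
- A reader might infer that choosing the test by observed shape inflates false positives. The simulation shows no material inflation; the cost is an effect measure that is not fixed.
- A reader might infer that statin use at entry is a ready covariate, since "All of these basic treatments will be detailed on the patient's medical record and CRF". That sentence in section 2.6 concerns background treatment during the trial, and statins are among the treatments all patients are to receive. The article does not state that statin use before entry is collected, and an in-trial yes/no item would hardly vary.

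**Conclusion.** The point holds as a free improvement. The comparison stated in section 2.10 is valid but less precise than the data allow, with no bias implied. At 49 per arm, prespecified baseline adjustment would raise power for LVEF from about 78-79% to somewhere between 82% and 97%. The position in that range depends on a correlation the protocol does not give; the gain is positive for any non-trivial correlation. The imbalance figures rest further on a baseline SD of about 5.98, borrowed from day 14. Separately, the shape-based rule leaves test and estimand open for each outcome and could move LVEF away from the mean difference on which the trial was sized.

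**What to change.** In section 2.10, replace the t-or-Mann-Whitney rule for the echo and lipid outcomes with the following:

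- **Model.** ANCOVA with treatment arm and the baseline value of the same variable, for LVEF, LVEDD, LVESD and each lipid.
- **Time points.** Day 14 for LVEF, the time point used for sizing, and the same model at 3 months.
- **Reporting.** Adjusted mean difference with 95% confidence interval.
- **Triacylglycerol.** Log-transform it (outcome and baseline) by advance decision, and report the back-transformed ratio with its interval.
- **Rank tests.** Sensitivity analyses only for these outcomes. Mann-Whitney remains available for angina attack counts and nitroglycerin tablets.

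Do not add a statin covariate on the strength of the present text. The enrolment of 55 per group need not change; since r is unknown, the gain is best kept as a margin.

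Cost: a change of wording before unblinding. The baseline measurements are already scheduled, and SPSS fits the model.

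### No outcome, time point or analysis set is named as deciding, although the trial is sized only on LVEF at 14 days; unadjusted P < .05 across nine outcomes does not hold the planned 2.5% error rate

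*Protocol article*

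**What the plan says.** **Outcomes (section 2.7).** There are three echocardiographic measures ("left ventricular end-diastolic diameter, left ventricular end-systolic diameter, and LVEF"), four lipids ("total cholesterol; triacylglycerol; low density lipoprotein cholesterol; high-density lipoprotein cholesterol") and two symptom measures ("The number of weekly attacks of angina pectoris; total amount of nitroglycerin tablets taken during the study period"). None is called primary or secondary, and the Abstract's list is also unranked.

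**Schedule (Table 1).** Cardiac function, lipids and nitroglycerin are ticked after baseline at 2 weeks and 3 months. Weekly angina attacks are ticked at 1 week, 2 weeks, and 1, 2 and 3 months.

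**Decision rule (section 2.10).** The only threshold is P < .05, at which "the difference was considered statistically significant". Sidedness is not stated. On analysis sets: "Efficacy evaluation will be determined by full analysis set and per-protocol set". On missing data: "Last observation carried forward method was used to estimate missing values of major variables". Which variables count as major is not said.

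**Sizing (section 2.4).** The calculation rests on the mean and "standard deviation of the left ventricular ejection fraction (LVEF) scores of patients 14 days after treatment", at one-tailed α = 0.025 and β = 0.20. It gives 49 per group, or 55 after a 10% drop-out allowance.

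**The concern.** The design and the analysis describe different trials. Section 2.4 describes a trial with one deciding test and a 2.5% chance of a false result in the drug's favour. Sections 2.7 and 2.10 describe a trial in which every outcome is judged by the same threshold and none takes precedence. Under the second description, a significant result on any one of nine outcomes could be presented as showing that the drug improves cardiac function or lipids, and nothing in the text would contradict that. Nor does the article say which analysis set prevails if the two disagree.

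What is at stake is the error rate attached to the main conclusion. The missing-data rule is affected too: carrying the last value forward is restricted to major variables, which presupposes a ranking that the article does not contain.

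**Working it through.** **1. The plan's own figure.** Inputs from section 2.4: means 53.13 and 49.78, SDs 6.18 and 5.78, one-sided α 0.025, power 0.80.

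- Difference = 53.13 − 49.78 = 3.35
- Pooled SD = √[(6.18² + 5.78²)/2] = 5.983
- n per group = 2 × [5.983 × (1.960 + 0.842)/3.35]² = 50.08, so 51
- Stated 49; 49/0.90 = 54.4, so 55 as stated

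The stated 49 is within two patients of the formula, which is close enough to confirm that the trial was sized for one test of LVEF at 14 days. One-sided 0.025 and two-sided 0.05 give the same n.

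**2. Number of comparisons.** From section 2.7 and Table 1, if each post-baseline visit is tested:

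- Cardiac function: 3 × 2 = 6
- Lipids: 4 × 2 = 8
- Angina attacks: 5
- Nitroglycerin: 2 (or 1, if read as one total over the study)
- Total: 21 (or 20) per analysis set

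**3. Chance of a false result with no drug effect.** Two-sided tests at 0.05 are assumed. Under independence:

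- Any significant result, 21 tests: 1 − 0.95²¹ = 65.9%
- Favouring the drug, 21 tests: 1 − 0.975²¹ = 41.2% (20 tests: 1 − 0.975²⁰ = 39.7%)
- Any significant result, nine outcomes at one visit: 1 − 0.95⁹ = 37.0%

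The outcomes are certainly correlated, but the article gives no correlations. The table assumes a common correlation r between normal test statistics, signed so that a positive value favours the drug.

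| One analysis set | r = 0 | r = 0.5 | r = 0.7 |
|---|---|---|---|
| 21 tests, any significant | 65.9% | 42.9% | 29.5% |
| 21 tests, favouring the drug | 41.2% | 21.6% | 14.8% |
| 20 tests, favouring the drug | 39.7% | 21.0% | 14.5% |
| 9 tests, any significant | 37.0% | 26.9% | 20.2% |

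A single common correlation is crude. A structured version assumes 0.5 to 0.9 for the same outcome over time, 0.3 to 0.7 within a domain and 0 to 0.3 across domains. It gives 34% down to 19% favouring the drug in one set.

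**4. Two further readings.**

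- *Either analysis set may be used.* With an assumed correlation of 0.95 between the two sets' results, the structured range becomes 41% down to 23%, and 50% with independent outcomes.
- *P < .05 is one-sided.* In one set the figure is 66% under independence and 54% down to 31% in the structured version.

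**5. Effect of naming one primary.** With LVEF at 14 days as the only deciding test, the false-positive rate in the drug's favour returns to 2.5%. Power for the planned effect is about 78–79% at 49 per group and 83% at 55. Keeping all 21 tests decisive with a Bonferroni threshold of 0.05/21 = 0.00238 would need about 97 evaluable patients per group for the same LVEF effect; power at 49 per group would be 39%.

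**The case against.** **The sizing shows the intended primary.** Section 2.4 uses LVEF at 14 days and nothing else, and section 2.10 speaks of major variables, so some ranking was evidently in mind. This stands as a sign of intent and makes the repair easy. It does not make LVEF decisive: no section says efficacy is judged on it, and the stated aim puts cardiac function and lipids side by side.

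**A condensed article leaves detail to other documents.** This holds for multiplicity procedures and the ordering of secondary outcomes, so their absence is no finding. It does not cover the deciding outcome and time point, which belong in the protocol. Here the outcomes section and the decision rule are both written out, and what they state treats all outcomes alike.

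**Table 1 is a measurement schedule, not a list of tests.** Fair: testing every visit separately is an inference, and 20 or 21 is conditional on it. Nine outcomes at one visit still give 20–37% for any significant result.

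**Using both analysis sets could mean both must agree.** Section 2.10 allows that reading, which would lower the error rate. The text does not say so, and the main range above is therefore for one set only.

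**Stronger readings that the documents do not support.** A reader might infer that a false efficacy claim is more likely than not. An efficacy claim needs a result in the drug's favour; under two-sided tests that chance is at most 41% in one set and about 50% with either set, both under independence. The 66% for two-sided tests counts results in either direction. The one-sided reading reaches 66% in the drug's favour only under independence, and section 2.10 does not fix sidedness. A reader might also treat the two sets as 42 independent tests, giving 88%; the sets share most of their patients, so that figure is wrong.

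**Conclusion.** The point stands as a gap between sizing and analysis. The article names no deciding outcome, time point or analysis set and judges nine unranked outcomes at unadjusted P < .05, while the sample size assumes a single LVEF test at one-sided 0.025. The chance of at least one false result favouring the drug in one set is about 15–41%, roughly 6 to 16 times the planned 2.5% (14.8/2.5 = 5.9; 41.2/2.5 = 16.5).

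This range rests on three assumptions that the article does not fix: two-sided tests, separate testing at each scheduled visit, and common correlations from 0.7 down to 0. The exact size depends on them, but none of the scenarios calculated here comes near 2.5%. It should be settled before unblinding, since a primary outcome named afterwards would not be credible.

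**What to change.** In sections 2.7 and 2.10:

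- Name LVEF at the end of the 14-day treatment (the 2-week visit), in the full analysis set, as the single primary comparison at two-sided 0.05, equivalent to one-sided 0.025 in the drug's favour.
- Make the per-protocol analysis supportive.
- Label all other outcomes and time points secondary, lipids included. Report them with estimates and 95% intervals, and do not present them as stand-alone proof of efficacy.

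Whether to test some secondary outcomes in a fixed order after LVEF, and in what order, is the sponsor's choice; the documents do not point to one.

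**Cost.** No change in sample size, because section 2.4 already covers this comparison. Section 2.9 requires ethics re-approval of any protocol change, so this is a formal amendment. The real price is that lipid and symptom results can no longer each carry a confirmatory claim, although lipids share the stated aim with cardiac function. If the sponsor wants a lipid outcome to be decisive as well, the sample size must be revisited, because section 2.4 covers LVEF only.
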